#### Secondary outcomes

The combinations of cardiovascular events are as follows:
Acute ST-induced myocardial infarction: Evidence of myocardial ischemia, one of the following factors, and the rise or fall of the biochemical marker values (preferably cardiac troponin) with at least one value above the 99th percentile upper reference limit: (A) symptoms of ischemia, (B) new or presumed new significant ST-segment–T wave (ST–T) changes or new left bundle branch block, (C) development of pathological Q waves in the electrogram (ECG), (D) imaging evidence of new loss of viable myocardium or new regional wall motion abnormality, and (E) identification of an intracoronary thrombus on angiography or autopsy.Other acute coronary syndromes: In patients experiencing ischemic symptoms (pain at rest, shortness of breath, press-like discomfort, or progressive exacerbation of the above symptoms), rest or use of nitrates will not relieve these symptoms. On ECG, a transient or persistent ST-segment offset of 0.1 mV or above in one or more leads is usually observed.Congestive heart failure requiring hospitalization: Normal venous reflux is a clinical syndrome characterized by tissue hypoperfusion and pulmonary or systemic circulatory congestion marked by a decrease in cardiac output and an increase in ventricular filling pressure due to the presence of a primary cardiac damage and cardiac insufficiency.Severe arrhythmias: cardiac arrest and resuscitation, ventricular fibrillation, persistent ventricular tachycardia, paroxysmal ventricular tachycardia, primary atrial fibrillation or atrial flutter, severe sinus bradycardia, and complete atrioventricular block after a percutaneous coronary intervention or coronary artery bypass grafting. The occurrence of combined cardiovascular events will be recorded in every visit within the period of 3 years.All-cause mortality. The mortality from any other cause will be registered. These events will be collated during the 3-year follow-up.eGFR decreased by 50%. The eGFR will be calculated at every visit. When the trial is completed, patients in both groups whose eGFR decreased by 50% will be judged as experiencing a renal event.

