### Eligibility criteria {10}

#### Participants

##### Inclusion criteria

According to the Kidney Disease: Improving Global Outcomes (KDIGO) guidelines, CKD refers to the abnormalities in the kidney structure or function or an estimated glomerular filtration rate (eGFR) of < 60 ml/min/1.73 m^2^ that persists for 3 months with or without kidney damage. The GFR was obtained by calculating the CKD-EPI using the following Cystatin C formula: eGFR=169 × Scr^-0.608^ × CysC^−0.63^ × Age^−0.157^ × (0.83 if female).Patients diagnosed with CKD stages 3–5 (non-dialysis dependent) aged 30–65 years (including those aged 30 and 65 years).Sex and ethnicity restrictions were not imposed.Patients without atherosclerosis in the common carotid artery as observed on the vascular ultrasound examination and no history of atherosclerosis in the carotid artery.An informed consent form from participants is required (Supplementary document).

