### Statistical analysis

#### Statistical methods for primary and secondary outcomes {20a}

For the primary outcome, the chi-square test will be performed to compare the occurrence rate of atherosclerosis at 1, 2, and 3 years of follow-up between the aspirin group and the placebo group. For the secondary outcome, the chi-square test will be performed to compare the combined cardiovascular events and all-cause mortality at 1, 2, and 3 years of follow-up between the aspirin group and the placebo group. Then, the decrease in eGFR will be computed using the value measured at the last follow-up minus the value measured at baseline; patients with a 50% decline in eGFR will be treated as patients who experienced an eGFR reduction of 50%. Similarly, the proportion of patients with an eGFR reduction of 50% between the aspirin group and the placebo group will be compared using the chi-square test. If the previous comparison did not reach a significant difference, the magnitude of decrease in eGFR between the two groups would be compared using two independent sample *t* tests or the Mann-Whitney *U* tests. In addition, multivariate competing-risk regression models will be used to assess the independent effect of treatments adjusted for age, sex, diabetes, serum lipid profiles, and phosphorus.

All statistical analyses will be performed using the SPSS software version 21.0 (IBM Corp., Armonk, NY, USA), and general data will be expressed as mean ± standard deviation. The variables with normal distribution and variance will be compared. One-way analysis of variance will be used for comparisons within groups. The SNK test will be used for multiple comparisons between groups. Pearson’s correlation analysis will be used for analyzing the correlation between variables. A nonparametric test will be used to analyze variables that do not meet the parameter test conditions. The Kruskal-Wallis *H* test or Mann-Whitney *U* test will be used for data comparison. Spearman’s correlation analysis will be used for correlation analysis. The chi-square test will be used for comparison. A *p* value of < 0.05 will be considered significant. A nonparametric test for multiple comparisons will be corrected using the Bonferroni method, *p* < 0.008, statistically significant safety analysis.

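### The other-ACS component of the combined cardiovascular outcome requires no objective evidence, so breathlessness from fluid overload or non-admitted heart failure can enter the composite

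*Protocol article*

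**What the plan says.** The Secondary outcomes section of the Protocol article lists the components of the combined cardiovascular outcome. The entry for other acute coronary syndromes has three elements:

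- Symptoms: "In patients experiencing ischemic symptoms (pain at rest, shortness of breath, press-like discomfort, or progressive exacerbation of the above symptoms".
- Non-relief: "rest or use of nitrates will not relieve these symptoms".
- ECG: "a transient or persistent ST-segment offset of 0.1 mV or above in one or more leads is usually observed".

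Two neighbouring entries set harder conditions. The MI entry requires "the rise or fall of the biochemical marker values (preferably cardiac troponin) with at least one value above the 99th percentile upper reference limit", together with one of items (A) to (E). The heart-failure entry is limited to "Congestive heart failure requiring hospitalization".

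Under Inclusion criteria the population is "Patients diagnosed with CKD stages 3–5 (non-dialysis dependent) aged 30–65 years". Under Statistical methods {20a}, "the chi-square test will be performed to compare the combined cardiovascular events and all-cause mortality at 1, 2, and 3 years of follow-up" between the two groups. The article gives no expected event rate, effect size or power for this composite.

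**The concern.** The first two elements of the other-ACS entry are conditions. The third says what is typical and excludes nobody. Taken literally, a listed symptom judged ischemic and not relieved by rest or nitrates is enough, and shortness of breath is one of the listed symptoms. Fluid overload and heart failure also produce breathlessness that persists at rest, and the trial enrols patients with CKD stages 3–5.

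This matters for two reasons. First, the list contradicts its own logic: it keeps out heart failure that did not lead to admission, yet the same episode can come in through the entry next to it. Second, the article's second objective asks whether therapy reduces cardiovascular events. If part of the count is unconfirmed breathlessness that aspirin does not affect, the estimated relative effect is weakened, and that part of the count rests on symptom judgement at 10 centres.

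**Working it through.** **Step 1: the components side by side**

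| Component | Symptoms | Objective evidence | Admission |
|---|---|---|---|
| MI | one of five options, (A) | marker rise or fall with a value above the 99th percentile: required | not required |
| Other ACS | required | ST offset of 0.1 mV or above: described as usual, not required | not required |
| Heart failure | syndrome described | none specified | required |

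Other ACS is the only one of the three with neither required objective evidence nor required admission. The article describes no rule for separating ischemic breathlessness from breathlessness of other cause. An outpatient episode of congestive breathlessness therefore fails the heart-failure entry for lack of admission, but can meet the other-ACS entry if the site regards the symptom as ischemic.

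**Step 2: direction and possible size**

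The plan has no figure for this outcome to reproduce. The 277 per arm in the Sample size section was derived for the primary outcome and is used here only as the arm size. Everything else in this step is assumed.

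*Illustration A.* Assume true 36-month rates of 10% (placebo) and 7% (aspirin), and x further percentage points in each arm that aspirin does not affect.

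- Observed risk ratio: RR = (7 + x)/(10 + x).
- Power (two-sided 0.05, pooled-variance form): Φ{[|p0 − p1|√n − 1.96√(2p̄q̄)] / √(p0q0 + p1q1)}, with n = 277.
- Worked case, x = 0: p̄ = 0.085; [0.03 × 16.643 − 1.96 × √0.15555] / √0.1551 = −0.695; Φ = 24.4%.

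| x (points) | Placebo v aspirin | RR | Power |
|---|---|---|---|
| 0 | 10% v 7% | 0.70 | 24.4% |
| 2 | 12% v 9% | 9/12 = 0.75 | 20.9% |
| 4 | 14% v 11% | 11/14 = 0.79 | 18.6% |
| 6 | 16% v 13% | 13/16 = 0.81 | 16.9% |

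The risk difference stays at 3 points by construction. The ratio moves towards 1, and power falls because the variance grows.

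*Illustration B.* Use the 20% relative reduction in CVD incidence that the Background cites for high-risk patients, an assumed true control rate p, and a false-positive proportion f acting independently of true events. The observed rate in each arm is 1 − (1 − true rate)(1 − f). For p = 10% and f = 5%: placebo 1 − 0.90 × 0.95 = 14.5%; aspirin 1 − 0.92 × 0.95 = 12.6%; RR = 0.87.

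| f | p = 10%: RR, power | p = 20%: RR, power |
|---|---|---|
| 0 | 0.80, 12.8% | 0.80, 23.1% |
| 2% | 0.83, 11.2% | 0.82, 21.2% |
| 5% | 0.87, 9.6% | 0.84, 18.9% |
| 10% | 0.91, 7.9% | 0.87, 15.9% |

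Both illustrations go the same way. Power for the composite is low even without misclassification, so the main harm is to the meaning of the estimate, not to a test that would otherwise have succeeded.

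**The case against.** **The entry is limited to ischemic symptoms.** A reader might infer that breathlessness from fluid overload automatically counts as a coronary event. The text does not say so: an investigator who attributes the symptom to congestion need not report it here. This stands. What remains is that shortness of breath is itself named as an ischemic symptom and nothing objective has to confirm ischemia. Such episodes can count; it is not shown that they will.

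**The composite is cardiovascular, not coronary.** From Illustration A a reader might infer that 4/14 = 29% of placebo events at x = 4 are contamination of a coronary endpoint. That uses the wrong benchmark. The composite deliberately includes heart failure and severe arrhythmias, so the other 10% need not be coronary, and heart failure entering by this route is still cardiovascular. For those episodes the error is a bypassed severity threshold and a wrong component label. This stands.

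**Frequency may be low.** The Exclusion criteria remove previous cardiovascular disease, including heart failure, and NYHA class III or IV. This is fair, and it is one more reason why the size is unknown.

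**Bias between arms.** A reader might also infer that symptom-only reports favour one arm. The Abstract and the blinding section describe a double-blind trial. The Trial design section calls it open, which is a separate contradiction to reconcile. The documents do not show differential reporting.

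**The article is condensed and its English is rough.** The ECG wording may be a loose rendering of an intended criterion, and adjudication detail may sit in a fuller document. But the article does state a definition for this component, and as stated it does not require the ECG change. The point concerns that stated rule, not missing detail.

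**Conclusion.** The point holds as a loosely fixed definition in a secondary outcome. The other-ACS entry can be met on ischemic symptoms alone, and it undercuts the hospitalization condition that the same list sets for heart failure. If the extra episodes are equally frequent in both arms and unaffected by aspirin, the risk ratio moves towards 1. Its size cannot be derived from the documents, because neither the cardiovascular event rate nor the misclassification rate is given. Under the assumptions shown, 2 to 6 added points move a true 0.70 to 0.75–0.81, and power falls from 24% to 17–21%. The primary outcome, its analysis and the sample size are untouched. The definition should be tightened because the change is cheap and the composite is otherwise hard to interpret; it does not threaten the trial's main conclusion.

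**What to change.** For outcome classification only, with no change to patient care, amend the other-ACS entry in Secondary outcomes:

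1. Count an episode as other ACS only if the ischemic symptoms come with at least one of: the ST offset already stated (0.1 mV or above); a biomarker rise or fall as in the MI entry; or imaging or angiographic evidence as in items (D) or (E) of that entry.
2. State whether marker-positive events without ST offset count under MI or under other ACS. The MI heading refers to ST-induced infarction, which leaves this unclear. Either choice keeps them in the composite.
3. Record symptom-only episodes outside the main composite and add them back in one sensitivity analysis.

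**Cost:** a sentence or two in the definition, one additional record category and one sensitivity analysis. **Downside:** some true unstable-angina episodes without objective evidence leave the main count. So do episodes during which no ECG was taken: the plan schedules ECGs only at 6, 12, 24 and 36 months, so the rule depends on records made at the time of the episode. The sensitivity analysis shows how much this matters.

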#### Safety outcomes

In the case of severe allergies, the drug should be discontinued immediately, and anti-allergy treatments and symptomatic treatments should be administered immediately.If a severe adverse event occurred, in addition to active treatment or rescue, the time, severity, duration, measures taken, and outcomes of serious adverse events should be recorded.If a treatment-related death occurred, the clinical study should be discontinued immediately, the event should be reported to the ethics committee of the clinical research unit as soon as possible, and the relevant information should be recorded and kept adequately in detail.All adverse events should be monitored until they are adequately resolved or until the patients’ condition stabilizes.

### Participant timeline {13}

The time schedule of enrollment, intervention assessments, and frequency of visits of all participants are shown in a schematic diagram (see the Research flow chart). The participants will be followed up at 0.5, 1, 2, 3, 4, 5, 6, 12, 24, and 36 months.

### Sample size {14}

#### Sample size estimation

The sample was calculated as follows: $$ n=\frac{{\left({z}_{\alpha}\sqrt{2\overline{pq}}+{z}_{\beta}\sqrt{p1q1+p0q0}\right)}^2}{{\left(p1-p0\right)}^2} $$

In this study, p0 and p1 represent the estimated exposure rates of the control group and the experimental group, respectively, while *Z*_α_ and *Z*_β_ indicate the standard positive distribution boundaries. In the table, when *α* or *β* is equal to 0.05, its value is 1.96; when *α* or *β* is equal to 0.01, its value is 2.58. In this study, the incidence of p0 is above 40% [8]. After the intervention, p1 is expected to decrease by 15% compared with p0 (p1 = 25%). Let *α* = 0.05 (both sides), and *β* = 0.10. The calculated minimum sample size is 251; if 10% of the cases were lost to follow-up, the calculated sample size would be 277 for each group, and approximately 554 patients will be included in the trial.

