The relationship between CKD platelet activation and accelerated atherosclerosis has drawn considerable attention in recent years. Other researchers and our previous studies have found that abnormal platelet activation is manifested by an increase in platelet reactivity in CKD patients and animal models [13–15]. Previous extensive population-based studies have shown that atherosclerosis is highly prevalent in CKD patients, thus increasing the risk of cardiovascular and all-cause mortality. CKD patients have more severe atherosclerosis than age- and sex-matched controls from the general population [6]. The NEFRONA study has indicated that the incidence rates of carotid atherosclerosis are 50.8% in patients with CKD and 69% in diabetic patients with CKD [16]. Currently, antiplatelet drugs are widely used to prevent CVD, especially intravascular thrombosis. Antiplatelet drugs can reduce CVD deaths by 15% and CVD incidence by 20% in high-risk patients [17]. The American Heart Association recommended that antiplatelet drugs can be used as a secondary prevention strategy for patients with high blood pressure, muscular atrophy, obesity, diabetes, or a family history of ischemic heart disease [17]. Although antiplatelet drugs have been shown to reduce the risk of CVD in patients with CKD, the benefits and evidence of using antiplatelet agents in CKD patients remain unknown. A previous meta-analysis showed that antiplatelet drugs could reduce the risk of myocardial infarction in patients with CKD but were not associated with all-cause and cardiovascular mortality [18]. Simultaneously, the SWEDEHEART study demonstrated that dual antiplatelet therapy could reduce the risk of all-cause mortality, stroke, and reinfarction in acute coronary syndrome patients with CKD [19]. Aspirin is widely used and recommended as the first-line antiplatelet drug in the clinical setting. However, a previous meta-analysis indicated that aspirin had no apparent benefits on the primary prevention of CVD in the CKD population [20]. Thus, the efficacy and safety of antiplatelet therapy, like aspirin, in patients with CKD remain controversial. The evidence is not considered robust as previous researches were small sample cohort studies and lacked large clinical randomized controlled (RCT) studies. In addition, CKD patients were excluded or only those with mild CKD (CKD stages 1–2) were recruited in previous extensive RCT studies to assess the efficacy of antiplatelet therapy. Thus, the use of antiplatelet therapy in patients with CKD has fundamental clinical significance. Therefore, a prospective RCT trial must be performed to determine the significance of antiplatelet therapy in CKD patients.

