## Discussion

Previous epidemic studies reported that the incidence rates of atherosclerosis in non-diabetic and diabetic CKD patients are 50% and 69%, respectively [16, 22]. The incidence of atherosclerosis in non-diabetic CKD patients was also proven by conducting an imaging analysis in a Korean study, which enrolled more than 3000 individuals without known CAD who underwent coronary computed tomography angiography. This study showed that 34.1% and 48.6% of the individuals with mild (eGFR 60–89 mL/min/1.73 m^2^) and moderate (eGFR 30–59 mL/min/1.73 m^2^) CKD had segment vessel stenosis and stenosis of ≥ 50%, respectively [23]. Aspirin has been shown to improve atherosclerosis in animal models. Aspirin-triggered lipoxins A4 (ATL4) is an effective anti-inflammatory mediator involved in inflammation regression. ATL4 reduced the macrophage infiltration and apoptosis in ApoE−/− mice with atherosclerosis in the aortic roots and thoracic aorta [24]. This indicates that aspirin can inhibit the expression of nuclear factor-kappa B1 and deactivate the cAMP signaling pathway to treat atherosclerosis [25]. Inflammation plays a vital role in the pathophysiology of atherosclerosis, and aspirin has significant anti-inflammatory properties. In Chai et al.’s study, orchidectomized Sprague-Dawley rats fed with a AIN-93 M casein-based control diet for 4 months developed atherosclerotic lesions. After treatment with aspirin (500 mg/kg) for 3 months, the fatty streak area was completely reversed, and the atherosclerotic lesions disappeared [26]. Therefore, the theoretical mechanism and arterial test of aspirin support its role in improving atherosclerosis.

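### The 40% control rate behind the sample size has no stated period or disease-free source population, so the power is not supported for the patients enrolled

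*Protocol article*

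**What the plan says.** **Control rate and effect.** Sample size estimation states "In this study, the incidence of p0 is above 40% [8" and "p1 is expected to decrease by 15% compared with p0 (p1 = 25" (per cent), so the planned comparison is 40% against 25%. The error rates are α = "0.05 (both sides), and" β = 0.10. It continues: "The calculated minimum sample size is 251", and "if 10% of the cases were lost to follow-up, the calculated sample size would be 277 for each group", 554 in all.

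**Who enters and what is counted.** The inclusion criteria ask for "Patients without atherosclerosis in the common carotid artery as observed on the vascular ultrasound examination" and no history of carotid atherosclerosis. Outcomes {12} and Table 1 define the primary outcome as the occurrence rate of atherosclerosis at 36 months.

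**Other frequencies in the article.** Background and rationale cites a cohort in which "the incidence rates of carotid atherosclerosis are 50.8% in patients with CKD and 69% in diabetic patients with CKD", in a paragraph about how prevalent atherosclerosis is in CKD. The Discussion repeats 50% and 69%, then says: "The incidence of atherosclerosis in non-diabetic CKD patients was also proven by conducting an imaging analysis in a Korean study". The figures from that study are 34.1% (mild CKD) and 48.6% (moderate CKD) of individuals who had stenosis on coronary CT. None of these figures has a time window. Reference [8], the source of the 40%, is cited elsewhere only in the Background, for plaque instability, with no rate.

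**The concern.** Because patients with common-carotid disease or a carotid history are kept out, p0 can only be the proportion of eligible patients who newly show atherosclerosis within 36 months. The section gives neither a period nor an at-risk population for the 40%, and no other part of the article gives an onset rate for patients who meet the entry criteria. The frequencies it does quote describe CKD patients in general, some of whom may already have lesions, and in the Discussion stenosis already present on a CT scan is called incidence.

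If onset in the enrolled patients is well below 40%, and aspirin's relative effect is the planned one, the trial has less power than stated. A non-significant result could then be taken as evidence that aspirin does not prevent atherosclerosis when there were too few onsets to tell.

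**Working it through.** **Inputs (Sample size estimation).** p0 = 0.40, p1 = 0.25, two-sided α = 0.05 (z = 1.96), β = 0.10 (z = 1.282), 251 per arm before dropout, 10% loss. Difference = 0.15; rate ratio = 0.25/0.40 = 0.625.

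**Step 1: the plan's own figure.** The printed formula is n = [z_α√(2p̄q̄) + z_β√(p1q1 + p0q0)]² / (p1 − p0)².

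- p̄ = 0.325, so √(2 × 0.325 × 0.675) = √0.43875 = 0.6624.
- √(0.1875 + 0.24) = √0.4275 = 0.6538.
- z_β = 1.282: (1.298 + 0.838)²/0.0225 ≈ 202.9, so **203 per arm** (216 with continuity correction).
- z_β = 1.645 (95% power): (1.298 + 1.076)²/0.0225 ≈ 250.4, so **251 per arm**.

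The stated 251 therefore corresponds to 95% power, not to β = 0.10. The 277 is 251 × 1.10 = 276.1, rounded up; 251/0.9 would give 279.

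**Step 2: power at other control rates.** The documents give no onset rate for eligible patients, so p0 is an assumed range. Inverting the formula at n = 251: z_β = [|p0 − p1|√251 − 1.96√(2p̄q̄)] / √(p0q0 + p1q1), with √251 = 15.843.

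Example with the ratio held, p0 = 0.30 and p1 = 0.1875: (0.1125 × 15.843 − 1.96 × 0.6072)/0.6020 = 0.984, power 83.7%.

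| p0 | p1 at ratio 0.625 | Power, ratio held | Power, 15 points held | Relative reduction implied by 15 points |
|---|---|---|---|---|
| 40% | 25.0% | 95.0% | 95.0% | 37.5% |
| 35% | 21.9% | 90.5% | 96.6% | 43% |
| 30% | 18.8% | 83.7% | 98.2% | 50% |
| 25% | 15.6% | 74.4% | 99.4% | 60% |
| 20% | 12.5% | 62.5% | 99.9% | 75% |

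With the ratio held, power is 90% at p0 ≈ 34.5% and 80% at p0 ≈ 28%.

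**Step 3: size needed for 90% at the same ratio.** Per arm 304, 385 and 507 at p0 = 30%, 25% and 20%. Dividing by 0.9 and doubling gives totals of 676, 856 and 1,128, against the planned 554.

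**The case against.** **The rate is called incidence and has its own citation.** That is so, and what reference [8] reports cannot be seen here. A reader might infer that the 40% is a prevalence taken from the background figures. The documents do not establish this: 40% equals none of the quoted values, those values come from other references, two of them concern coronary arteries, and the 34.1% is for eGFR 60–89, outside the trial population. What stands is narrower: the plan does not show that the 40% is a 36-month onset rate in eligible patients.

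**Onset may be high in these patients.** They have CKD stages 3–5 and diabetes is not excluded. The entry scan criterion names only the common carotid, whereas the outcome scan covers both carotid arteries and counts plaque and intima-media thickness as indicators. Each of these could raise the observed rate, so the enrolled group cannot simply be called low-risk. None of them supplies a figure.

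**The design has slack.** It does: 251 against the 203 needed. The table above already includes that slack, which runs out below about 34.5% if the ratio is held.

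**The planned effect is 15 points, and at that difference power rises as p0 falls.** Correct. The price is a relative reduction of 50% at p0 = 30% and 75% at 20%, which the article does not argue for.

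**The study is described as exploratory and as a pilot.** This softens the consequences of a null result, but the section still fixes N on a formal power claim.

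**Conclusion.** The point holds as a gap in justification. The 40% has no stated period and no disease-free source population, and nothing else in the article supports it for patients meeting the entry criteria, so the power claim is unsupported for them.

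A reader might go further and conclude that the trial is underpowered. The documents do not show that. At 40% against 25% the planned number gives about 95% power, more than the 90% that β = 0.10 implies, and it stays at or above 90% down to p0 of about 34.5%. Loss of power below that depends on two assumptions: that true onset is lower, and that the rate ratio of 0.625, not the 15-point difference, carries over. Under both, power is 84% at p0 = 30%, 74% at 25% and 63% at 20%. The article gives no time course from which a likelier p0 could be derived.

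**What to change.** Keep N at 554 and change the text.

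1. In Sample size estimation, define p0 as the 36-month new-onset proportion in patients meeting the entry criteria, and say what the cited source reports in those terms, or that the 40% is an assumption.
2. State whether the expected effect is an absolute difference or a ratio, so that it is clear what carries over if p0 is not 40%.
3. Replace the single power claim with a table over p0 such as the one above, and correct the mismatch between β = 0.10 and 251 per arm.
4. Pre-specify that blinded pooled onset at the scheduled 12- and 24-month scans is read against the table. With the ratio held, the 36-month pooled proportion is p0 × (1 + 0.625)/2: 32.5% at p0 = 40%, 28.0% at 34.5%, 24.4% at 30% and 16.3% at 20%. Say how the earlier scans relate to these values.
5. Reconcile this with Interim analyses {21b}, which says not applicable, and the stopping-guidelines section, which refers to blinded interim analyses by the DSMB.
6. State that a null result under low pooled onset is reported as inconclusive, with the 95% confidence interval for the difference.

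This costs wording and one table, with no extra patients or scans. The stated power becomes conditional and may look less favourable. Blinded pooling also cannot separate a low p0 from a strong effect: a pooled 22.5% fits 30% against 15% (power 98%) or about 27.7% against 17.3% (power just under 80%). The confidence interval at the end therefore has to carry the interpretation.

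### The 251 per arm is the 95%-power sample size, not the 90% that the stated β of 0.10 implies; the error is conservative and needs only a restatement.

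*Protocol article*

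**What the plan says.** The section Sample size {14} of the protocol article prints the usual two-proportion formula, with a pooled variance under the null hypothesis and separate variances under the alternative. It takes a control rate p0 of 40% (worded as above 40%) and an aspirin rate p1 of 25%.

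The error rates are explicit: "Let *α* = 0.05 (both sides), and *β* = 0.10". The normal quantiles come from one rule for both: "when *α* or *β* is equal to 0.05, its value is 1.96; when *α* or *β* is equal to 0.01, its value is 2.58". No quantile is printed for 0.10.

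The result is given as: "The calculated minimum sample size is 251; if 10% of the cases were lost to follow-up, the calculated sample size would be 277". Both figures are per arm, and the total is put at about 554.

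**The concern.** All the inputs needed for the formula are in the section, so the result should be reproducible, and it is not. A β of 0.10 means 90% power, for which z_β is 1.282. The rule quoted above gives β a two-sided quantile, although the type II error sits in one tail. If that rule was carried to β = 0.10, the value used was 1.645, and the sample size was then computed for a higher power than the one stated.

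What is at stake is the accuracy of the stated power and the reason for the number randomised. Anyone who takes β = 0.10 at face value will believe that 554 patients are needed for 90% power.

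**Working it through.** **Inputs** (all from Sample size estimation): p0 = 0.40, p1 = 0.25, two-sided α = 0.05 (z_α = 1.96), β = 0.10, loss 10%, equal groups.

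**Formula as printed:** n per arm = [z_α √(2 p̄ q̄) + z_β √(p1q1 + p0q0)]² / (p1 − p0)²

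- p̄ = (0.40 + 0.25)/2 = 0.325 and q̄ = 0.675, so √(2 × 0.325 × 0.675) = √0.43875 = 0.6624
- p1q1 + p0q0 = 0.1875 + 0.2400 = 0.4275, with square root 0.6538
- (p1 − p0)² = 0.15² = 0.0225
- first term: 1.96 × 0.6624 = 1.298

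**Reproducing the plan's 251.** With z_β = 1.645: (1.298 + 1.645 × 0.6538)² / 0.0225 = 250.4, rounded up to 251. This matches exactly. The one-sided quantile for 0.05 is 1.645; it is also the two-sided quantile for 0.10.

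**With the stated β = 0.10.** With z_β = 1.282: (1.298 + 1.282 × 0.6538)² / 0.0225 = 202.9, rounded up to 203.

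**Other routes to 251 at 90% power.** None reaches it:

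| Variant | n per arm |
|---|---|
| Printed formula | 203 |
| Continuity correction | 216 |
| Unpooled variance | 200 |
| Arcsine | 203 |
| One-sided α | 166 |
| p0 above 40%, 15-point difference kept | at most about 232 |
| 15% read as a relative reduction (40% v 34%) | 1359 |

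The last reading is in any case excluded by the stated p1 of 25%.

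**Loss to follow-up, stated β.** 203/0.90 = 225.6, so 226 per arm and 452 in total. Against the plan: 554 − 452 = 102 more patients.

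**Loss to follow-up, as printed.** 251 × 1.10 = 276.1, so 277. Dividing instead gives 251/0.90 = 278.9, so 279. With 277 randomised, 277 × 0.90 = 249.3, so 249 evaluable.

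**Power for 40% v 25% at two-sided 0.05.** Power = Φ([0.15 √n − 1.298] / 0.6538):

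| Evaluable per arm | Power |
|---|---|
| 203 | 90.0% |
| 249 (277 less 10%) | 94.9% |
| 251 | 95.0% |
| 277 (no loss) | 96.7% |

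**The case against.** The strongest reply is that the number can be traced and does no harm. The section states its z convention, and under that convention β = 0.10 leads to 1.645 and to 251. The trial has more power than it claims, and no endpoint, test or decision rule changes.

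Most of this stands. The origin of 251 can be worked out, although 1.645 has to be inferred because the quantile for 0.10 is not printed. It does not make the stated β right: in this formula z_β = 1.645 gives 95% power, whatever table it was read from.

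Three stronger readings are tempting, and the document does not support them.

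- **That the trial is underpowered, or that a null result would be less informative than claimed.** The opposite holds on the plan's own assumptions: power is about 95% against a stated 90%.
- **That the loss allowance is a second error of substance.** Multiplying by 1.10 instead of dividing by 0.90 costs 2 patients per arm and moves power from 95.0% to 94.9%. The article also calls 554 approximate.
- **That the 40% control rate is unsound because no time horizon is attached.** It rests on a cited source that is not shown, so whether that source gives 36-month onset in plaque-free patients cannot be judged. The 50.8% and 69% in the Background are not used in the calculation. A fall in power at lower control rates depends on the effect assumed. With 249 per arm and a constant relative reduction of 37.5% (assumption), power is 83% at a control rate of 30% and 62% at 20%. With the 15-point difference held constant (also an assumption), it is 98% and over 99.9%. Neither version demonstrates a shortfall.

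**Conclusion.** The point holds as a misstatement of β and therefore of power. The stated inputs give 203 evaluable patients per arm; the reported 251 is the figure for β = 0.05. The planned 554 gives 94.9% power after 10% loss, about 5 percentage points above what the article states, and 102 patients more than its stated β requires.

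This rests on the printed formula and on 40% v 25% at two-sided 0.05. That a two-sided quantile was used for β is an inference, but the exact match at 1.645 and the z rule in the same paragraph support it well. The error is conservative. It should be corrected because the figure justifies the size of the trial, but it does not threaten the validity of the primary comparison.

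**What to change.** In Sample size estimation, choose one of two routes.

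1. **Keep 554.** State β = 0.05 (95% power, z_β = 1.645). A possible wording: 251 evaluable patients per arm give 95% power to detect 40% v 25% at two-sided α = 0.05; 277 randomised per arm leave 249 after 10% loss, with power 94.9%.
2. **If β = 0.10 was intended,** print 203 per arm, 226 per arm after 10% loss, and 452 in total.

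Under either route, correct the sentence on z values: 1.96 belongs to two-sided α = 0.05, and β takes one-sided quantiles (1.282 for 0.10, 1.645 for 0.05).

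Minor note: if exactly 251 evaluable per arm is wanted after 10% loss, the figure is 279 per arm (558 in total). This is not needed to keep the power at about 95%.

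Cost: the first route is a wording change in one section, with no change in patient numbers. The second lowers the stated target by 102.
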